**Methods and analysis:**

BioHEART-CT is a longitudinal, prospective cohort study, aiming to recruit 5000 adult patients undergoing clinically indicated CTCA. After informed consent, patient data, blood samples and CTCA imaging data are recorded. Follow-up for all patients is conducted 1 month after recruitment, and then annually for the life of the study. CTCA data provide volumetric quantification of total calcified and non-calcified plaque, which will be assessed using established and novel scoring systems. Comprehensive molecular phenotyping will be performed using state-of-the-art genomics, metabolomics, proteomics and immunophenotyping. Complex network and machine learning approaches will be applied to biological and clinical datasets to identify novel pathophysiological pathways and to prioritise new biomarkers. Discovery analysis will be performed in the first 1000 patients of BioHEART-CT, with validation analysis in the following 4000 patients. Outcome data will be used to build improved risk models for CAD.

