### Objectives

#### The primary objectives of the BioHEART-CT study are

To identify new biomarkers to assist in early CAD risk identification and stratification.To identify new mechanistic pathways that may be targeted with novel therapeutic strategies to abrogate CAD risk.

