**Figure 4 F4:**
[figure not shown]
Overview of the analytic approach. CAD, coronary artery disease; RF, risk factor; SMuRF, standard modifiable cardiovascular risk factor.

Biomarker and risk factor data analysis will depend on the specifics of the assay or investigation performed. Generally, continuous variables will be presented as means (with SD) or medians (with IQRs), categorical variables as proportions (%) with X^2^ or Fisher’s exact test used to determine differences between groups. Hazard ratios for a 1 SD increase in a biomarker, after log transformation to remove effects of outliers, on MACE will be obtained from weighted Cox regression models. All p values reported will be two sided, with the 5% threshold used to determine significance.

For testing the prognostic value of prioritised biomarkers, and assuming a C-statistic of 0.75 for traditional risk factors, we estimate that we will require 705 participants to detect a C-statistic of 0.85 with p=0.05, power of 80% and an event rate of 20%. Models developed with different sets of variables and biomarkers and C-statistics for 1-year risk will be determined and compared. The model’s ability to discriminate and reclassify 1-year risk will be assessed using the integrated discrimination index and the net reclassification improvement.

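### Discrimination and reclassification are tied to 1-year risk only, so MACE collected after year 1 cannot enter the model comparisons

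*Protocol article*

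**What the plan says.** The Data analysis plan names one horizon, twice. For discrimination: "Models developed with different sets of variables and biomarkers and C-statistics for 1-year risk will be determined and compared". For the remaining measures: "The model’s ability to discriminate and reclassify 1-year risk will be assessed using the integrated discrimination index and the net reclassification improvement". No other horizon is given for any comparison of models.

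The same section plans hazard ratios per 1 SD of biomarker that "on MACE will be obtained from weighted Cox regression models", with no 1-year limit. It also sizes the prognostic comparison: "assuming a C-statistic of 0.75 for traditional risk factors, we estimate that we will require 705 participants to detect a C-statistic of 0.85". The inputs to that calculation are a 5% significance level, 80% power and a 20% event rate, and no time period is attached to the event rate. Testing is fixed by "All p values reported will be two sided, with the 5% threshold used to determine significance".

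On follow-up, the Abstract says: "Follow-up for all patients is conducted 1 month after recruitment, and then annually for the life of the study". The section on patient data collection adds record linkage and independent adjudication of events. The strengths and limitations box says that longitudinal outcomes will feed the risk models, and a secondary objective is a risk score that predicts cardiovascular events better. Neither mentions 1 year.

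**The concern.** The cohort pays for yearly contact, record linkage and adjudication over an open-ended period, but the measures that decide whether a biomarker improves a risk model stop at 12 months. Followed as written, an infarction in month 13 or year 4 contributes nothing to the C-statistic, IDI or NRI as an event; that patient counts as event-free at the horizon. The precision of those measures depends mainly on the number of events, so a short window can cost power that the collected data would supply.

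The sample size adds a second difficulty. It rests on a 20% event rate with no horizon, while the analysis it supports is at 1 year. A reader cannot tell whether 705 participants would yield the intended number of events within that year.

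**Working it through.** **1. Reproduce the plan's figure.** Inputs from the Data analysis plan: C-statistics 0.75 and 0.85, two-sided 5%, power 80%, event rate 20%. Binormal (Obuchowski) variance per event, with k = non-events/events and a = 1.414·Φ⁻¹(C):

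V = 0.0099·exp(−a²/2)·[(5a² + 8) + (a² + 8)/k]

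With k = 4: a = 0.954 and 1.466, V₁ = 0.0928, V₂ = 0.0720. Let r be the correlation between the two estimated C-statistics. Then

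events = [1.96·√(2V₁(1−r)) + 0.842·√(V₁ + V₂ − 2r√(V₁V₂))]² / 0.10²

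At r = 0: (1.96 × 0.431 + 0.842 × 0.406)² / 0.01 = 140.7, so 141 events, and 141/0.20 = **705**. The figure reproduces exactly, and it implies two uncorrelated C-statistics.

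**2. Share of MACE in year 1.** The protocol gives no annual rate. Assume a constant annual risk p and complete follow-up to year T: share = p / [1 − (1−p)^T]. For p from 0.5% to 5%:
- T = 2: 50–51%
- T = 3: 34–35%
- T = 5: 20–22%

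**3. Power at 1 and 5 years for the protocol's contrast.** Take the 4000 validation patients and assume 1% per year. Events: 4000 × 0.01 = 40 at 1 year; 4000 × (1 − 0.99⁵) = 196 by 5 years. Power is

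Φ{[0.10·√events − 1.96·√(2V₁(1−r))] / √(V₁ + V₂ − 2r√(V₁V₂))}

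At 1 year with r = 0: V₁ = 0.0794, V₂ = 0.0637, giving Φ[(0.632 − 1.96 × 0.398)/0.378] = Φ(−0.39) = 0.35. In brackets is the variant that uses the alternative variance in both terms. It gives slightly higher power, but needs 130 events and 130/0.20 = 650 participants, so it does not reproduce 705.

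| r | 1 year (40 events) | 5 years (196 events) |
|---|---|---|
| 0 | 0.35 (0.39) | 0.94 (0.95) |
| 0.5 | 0.62 (0.65) | about 1.00 |
| 0.8 | 0.95 (0.96) | about 1.00 |

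Other assumed 1-year risks, r = 0, formula that reproduces 705: 0.5% gives 0.19, 2% gives 0.61, 3% gives 0.79, 5% gives 0.95.

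A smaller gain, 0.75 vs 0.80, at 1% per year: about 0.12 at 1 year against 0.41 at 5 years (r = 0), and about 0.42 against 0.97 (r = 0.8).

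**4. What the undated 20% could mean** (0.75 vs 0.85, r = 0, constant hazard):
- A 1-year rate: 4000 × 0.20 = 800 events in year 1, power about 1.00.
- A 5-year cumulative rate: 1-year risk 1 − 0.80^(1/5) = 4.4%. At 1 year, 705 patients give 31 events and power 0.27; 4000 give 175 events and power 0.92.
- A 10-year cumulative rate: 1-year risk 2.2%. At 1 year, 705 patients give 16 events and power 0.15; 4000 give 88 events and power 0.66.

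**The case against.** One year is a coherent horizon. Nearly every participant can reach it while recruitment is still open, and nothing in the text forbids a longer one. The article condenses a fuller protocol, and the choice of a particular estimator could reasonably be left to that document. This is a good reason to keep the 1-year results. It does not remove the point, because the article does state a horizon, gives it for all three measures, and gives no other.

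A reader might go further and infer that the plan discards most MACE and most of the power of the prognostic models. The protocol does not support that:
- Whether most MACE fall after year 1 depends on follow-up length and hazard shape, and neither is given. Under a constant hazard, year 1 still holds about half of the events seen by year 2, and front-loaded events would raise that share.
- The Cox hazard ratios carry no 1-year limit, and a model fitted to all follow-up can still produce 1-year predictions. The restriction falls on the performance measures, not on model development.
- With strongly correlated models, or a 1-year risk of 5% or more, the stated 0.10 gain is well powered at 1 year.

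A reader might also argue that year 1 is the period most distorted by treatment prompted by the scan, or that the objective "To identify new biomarkers to assist in early CAD risk identification and stratification" demands a long horizon. The protocol gives no data on the first. On the second, the word early there describes when risk is identified; no prediction window is set.

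**Conclusion.** The point holds in a limited form. As written, MACE after year 1 can enter the hazard ratios but not the C-statistic, IDI or NRI comparisons, although those events are followed and adjudicated.

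The size of the loss is uncertain because it depends on a MACE rate and a between-model correlation that the protocol does not give. At an assumed 1% per year in 4000 patients, 1-year power for 0.75 vs 0.85 ranges from 0.35–0.39 (r = 0) to 0.95–0.96 (r = 0.8), against at least 0.94 at 5 years. Power at 1 year is lower still for smaller gains. If 20% is the 1-year rate, the stated comparison has ample power, and what remains is the unused later events.

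These figures assume a constant hazard, complete follow-up to the horizon, and the same C-statistics at 1 and 5 years. This is an inexpensive improvement to the plan, not a flaw that invalidates it.

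**What to change.** In the Data analysis plan:
1. Add a censoring-adjusted time-to-event C-statistic (for example Uno's C) over all accrued follow-up.
2. Add censoring-adjusted IDI and NRI at longer horizons with adequate numbers at risk, for example 3 and 5 years.
3. Keep the 1-year results alongside.
4. State the horizon to which the 20% event rate behind the 705 applies. If it is not 1 year, restate the requirement for the 1-year comparison.

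The cost is revised wording and a little more analysis. No new patients, visits or data items are needed. The drawback is that fixed 3- and 5-year results mature later for the last recruits; the C-statistic over accrued follow-up largely avoids this.

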## Discussion

Three main advances have been applied in the design of BioHEART-CT that provide a strategic advantage compared with previous studies which also used unbiased approaches to discover novel mechanisms and markers of atherosclerosis. First, this study includes quantification and characterisation of plaque (and the absence of plaque) by CTCA and advanced imaging algorithms, improving the power of the study compared with those that relied on CAD-related clinical events. Second, this study integrates high through-put, state-of-the-art multiomic molecular phenotyping with comprehensive clinical data and follow-up. And third, the study brings together a global team of biologists and bioinformaticians with complementary approaches and perspectives to enhance the likelihood of new discoveries.

In previous CAD studies, healthy controls were often defined as patients who had not had a cardiac event, or who had non-obstructive atherosclerosis on invasive coronary angiography which has limited utility in identifying extraluminal plaque. As CAD often remains silent until it is very advanced, those without a myocardial infarction could have quite extensive disease and still be considered a ‘healthy’ control. In BioHEART-CT, we have the capability to use our CTCA subgroup to more precisely phenotype subjects, allowing the accurate creation of a group of healthy controls which truly have no atherosclerotic disease present in their coronary arteries. This group of healthy patients can be used as a comparator for those with various stages of disease, reducing confounding factors and enhancing the capacity to detect real differences in biology.

Additionally, CTCA phenotyping can be used to analyse plaque composition in detail. Using scoring systems such as Gensini,^25^ severity scores can be generated for each individual. We have also developed a modified Gensini score as outlined above, which gives different weight to the presence of older, calcified plaque and newer, more biologically active non-calcified plaque. Automated detection of soft plaque shows promise as a scalable, reproducible method to add value to existing CTCA analysis.^26^ In identifying patients with high levels of active atherosclerotic plaque, we can create groups enriched for this biological feature, with and without traditional risk factors. This will better enable us to detect novel mechanisms of CAD in those with unexplained susceptibility.

Our unbiased approach to cardiovascular risk factor discovery, applying the advantages of high throughput multiomics platforms, improved quantification of plaque and its characteristics, and advanced statistical bioinformatics, provides a high chance of discovering previously unidentified mechanisms and markers of disease. We have recently discussed the advantages of integrating multiomics over isolated genomics studies for the complex disease process of atherosclerosis,^27^ and this will be particularly beneficial in such well-phenotyped groups.

Molecular markers found to be associated with atherosclerosis may be direct drivers of disease, or result from the plaque and dysregulated vascular physiology. The closer the marker is to the underlying biology, the more likely it will be to be useful in clinical practice, transforming our ability to identify early vascular disease and susceptibility above and beyond traditional risk calculators. We are well placed to take any markers and their surrounding pathways into preclinical cellular and animal models to determine causality and/or mechanisms for association. This will help prioritise markers for testing in prospective clinical trials for their value in improving patient care and outcomes, as well as identifying potential novel signalling pathways involved in disease that may be therapeutic targets.

In conclusion, BioHEART-CT is a study created in response to patients who have had heart attacks and their frequent question from the cardiac catheter laboratory table- ‘Why me?’. While it is imperative that we measure and treat well-established risk factors for atherosclerosis, this approach misses a substantial group of patients with CAD who are not identified as being at risk. We hypothesise that major mechanisms for atherosclerosis remain to be discovered and can be unravelled by comprehensive molecular characterisation, combined with powerful bioinformatic analyses. BioHEART-CT’s platforms and team are well positioned for discovering new markers and mechanisms of disease, and to take these both back to the bench to unravel new biology, as well as through to prospective clinical trial to test prognostic and clinical utility.

## Ethics and dissemination

Informed consent is obtained from the participants prior to enrolment, and the data and samples are deidentified and managed entirely anonymously with the exception of the required information for follow-up phone calls. The most significant risk to the patients in this study is that of venesection, with a possible consequence of mild bruising or superficial infection. Participants can withdraw from the study at any time and this will not have any impact on their clinical care.

The results of this study will be published in peer-reviewed journals and presented at domestic and international scientific meetings. No identifiable information will be published.
